## Abstract

**Background:**

Drug related problems (DRPs) are common among elderly patients who are discharged from the hospital and are using several drugs for their chronic diseases. Examples of drug related problems are contra-indications, interactions, adverse drug reactions and inefficacy of treatment. Causes of these problems include prescription errors and non-compliance with treatment. The aim of this study is to examine the effect of *medication review *and *cognitive behaviour therapy *of discharged patients by community pharmacists to minimize the occurrence of drug related problems.

**Methods/Design:**

A randomized controlled trial will be performed. Community pharmacists will be randomized into a control group and an intervention group. 342 Patients, aged over 60 years, discharged from general and academic hospitals, using five or more prescription drugs for their chronic disease will be asked by their pharmacy to participate in the study.

Patients randomized to the control group will receive usual care according to the Dutch Pharmacy Standard. The medication of patients randomised to the intervention group will be reviewed by the community pharmacist with use of the national guidelines for the treatment of diseases, when patients are discharged from the hospital. The Pharmaceutical Care network Europe Registration form will be used to record drug related problems. Trained pharmacy technicians will counsel patients at home at baseline and at 1,3,6,9 and 12 months, using Cognitive Behaviour Treatment according to the Theory of Planned Behaviour. The patient's attitude towards medication and patient's adherence will be subject of the cognitive behaviour treatment. The counselling methods that will be used are *motivational interviewing *and *problem solving treatment*. Patients adherence towards drug use will be determined with use of the Medication Adherence Report Scale Questionnaire. There will be a follow-up of 12 months.

The two primary outcome measures are the difference in occurrence of DRPs between intervention and control group and adherence with drug use. Secondary endpoints are attitude towards drug use, incidence of Re-hospitalisations related to medicines, functional status of the patient, quality of life and the cost-effectiveness of this intervention.

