### Study procedures

#### Intervention group

##### Medication review

The medication of patients in the intervention group will be reviewed by the community pharmacist using the full record of prescription only drugs which were dispensed by the patients' pharmacy and the patients medication evaluation profile. This profile shows when the patients has obtained his medication from the pharmacy. The GP will be consulted by telephone for details about indications for drugs and results from laboratory tests. When prescribed by a medical specialist, details about the indication for the drug will be obtained from the specialist, who will be consulted by the community pharmacist. The National guidelines for treatment of diseases will be used by community pharmacists as a method for performing medication review.

The Pharmaceutical care network Europe DRP-score form will be used to record drug problems. Each drug will be evaluated on adverse reactions, drug choice problems, dosing problems, drug use problems, drug-interactions or other problems. Causes for drug related problems will be assessed and interventions will be made. During the medication review the patient will be involved as a full partner. Any changes made will be communicated with the patient. This method for medication review will be pilot tested before use.

The occurrence of drug related problems will be discussed with the GP. The result may be an adaptation of the drug regimen. The medication review will take 10-30 minutes per patient and will depend on the complexity of the medication regimen and problems detected.

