#### Adherence with drug treatment

The 5-item self-report Medication Adherence Rating Scale (MARS) will be used to assess medication adherence [24].

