### Sample size

The primary outcome measure is the result of the medication review and patient counselling on the occurrence of DRPs. Based on previous studies it is estimated that the percentage of DRP in the patients of control pharmacists is 30%. It is estimated that the intervention reduces the number of preventable DRP with one third (33%). With a type 1 error of 0.05, a power of 80%, and a ration of one between both groups of patients, multilevel randomisation resulting in a loss of power of 15%, a total of 342 patients is needed to show a statistically significant difference. The estimated number of patients fulfilling the criteria and willing to participate is 4 per pharmacy per month. With an actual recruitment time of 6 months, and about 20 participating pharmacies, the number of 342 patients will be achieved.

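### Two primary outcomes are declared, but the 5% error and 80% power are set for DRPs alone; with two primaries, one of those figures does not hold

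*Protocol article*

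**What the plan says.** The Abstract (Methods/Design) of the protocol article states: "The two primary outcome measures are the difference in occurrence of DRPs between intervention and control group and adherence with drug use". The Outcome Measures section agrees by its order. Adherence has its own heading after the primary outcome heading and before the secondary outcomes, with the line: "The 5-item self-report Medication Adherence Rating Scale (MARS) will be used to assess medication adherence".

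The Sample size section uses the singular: "The primary outcome measure is the result of the medication review and patient counselling on the occurrence of DRPs". It then gives the design parameters: "With a type 1 error of 0.05, a power of 80%, and a ration of one between both groups of patients". The control rate is 30%, reduced by one third, and the result is "multilevel randomisation resulting in a loss of power of 15%, a total of 342 patients is needed to show a statistically significant difference". All of this refers to DRPs. The section gives no effect size, standard deviation, error allocation or power for adherence.

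The Objectives section makes the effect on DRPs the objective. It words the hypothesis as fewer DRPs together with better compliance, and does not list adherence among the secondary objectives. The Analyses section plans multilevel regressions of the outcome measures with 95% confidence intervals. No section says whether success needs one outcome or both.

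**The concern.** A trial with two primary outcomes needs a rule for turning two results into one conclusion. The Sample size section is written as though the question does not arise, because it has one outcome and one 5% error. A reader of the Abstract would expect two.

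What is at stake is the meaning of a positive result. If adherence improves on MARS and DRPs do not change, the Abstract would allow the trial to be reported as positive on a primary outcome. The Sample size section would call the same result negative on its only primary outcome. The 5% error and 80% power describe the trial's main claim only if the Sample size section is the one that is right.

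**Working it through.** **Inputs.** Number of primary outcomes: two (Abstract; order of the Outcome Measures section) or one (Sample size). Type 1 error 0.05, power 80%, allocation 1:1, DRP rate 30% reduced by one third, 15% allowance for clustering, 342 in total (all from Sample size). Sidedness is not stated, and I assume two-sided. The correlation between the two test statistics is not given, so I show a range.

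**The plan's own figure.** For 30% against 20%, two-sided 0.05 and 80% power, with pooled variance under the null:

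n per arm = [1.96·√(2·0.25·0.75) + 0.8416·√(0.30·0.70 + 0.20·0.80)]² / 0.10² = 294 after rounding up, or 588 in total before any clustering allowance.

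I could not reproduce 342 as a total. The unpooled, arcsine, continuity-corrected and one-sided variants do not give it either; the lowest one-sided total is 458. It does match a number per arm: with 30% against 20.1%, the unpooled formula gives 297, and 297 × 1.15 = 341.55, which rounds up to 342. That is a separate point. It matters here only because it shows that the calculation concerns DRPs and nothing else, and because it affects the cost of the fix.

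**Reading 1: either outcome suffices.** With each test at two-sided 0.05 and both null hypotheses true:

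- Independent tests: 1 − 0.95² = 0.0975. The upper bound at any correlation is 0.05 + 0.05 = 0.10.
- Correlated tests: 1 − P(|Z₁| ≤ 1.96 and |Z₂| ≤ 1.96) under a bivariate normal with correlation ρ.
- False claims of benefit only (0.025 each): 1 − P(Z₁ ≤ 1.96 and Z₂ ≤ 1.96). At ρ = 0 this is 1 − 0.975² = 0.0494.

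| ρ | Any false claim, two-sided | False claim of benefit |
|---|---|---|
| 0 | 9.75% | 4.94% |
| 0.3 | 9.51% | 4.76% |
| 0.5 | 9.07% | 4.54% |
| 0.7 | 8.35% | 4.17% |
| 0.9 | 7.04% | 3.52% |

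The single-test values are 5% and 2.5%.

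**Reading 2: both outcomes required.** The chance of a false overall claim is at most 5%, so nothing is inflated. Power for the joint claim cannot exceed the smaller of the two powers, and the power for adherence cannot be computed from the article. As an illustration only, if each had 80% power and the tests were independent, joint power would be 0.80 × 0.80 = 64%.

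**Reading 3: DRPs alone are primary.** The 0.05 and the 80% then refer to the right outcome, but the Abstract and the placing of adherence among the outcomes are wrong.

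Each reading therefore contradicts something on the page.

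**The case against.** The strongest reply is that the article nowhere says either outcome is enough. Its hypothesis joins fewer DRPs and better compliance with an *and*, as does the Abstract's Discussion. If both are required, there is no inflation. This stands to the extent that the 9-10% figure must be conditional. It does not remove the point: the hypothesis says what the intervention is expected to do and is not a testing rule, and under the joint reading the 80% power fails instead.

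Two further replies lower the size. The two-sided figure includes false findings of harm; counting benefit only, the error goes from 2.5% to at most about 4.9%. The outcomes are also probably correlated, since the Background names non-compliance as a cause of DRPs, and correlation reduces the inflation.

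A multiplicity rule could also sit in a statistical analysis plan or full protocol that is not shown, so its absence from an article is no fault. That is fair. What remains is the conflict between two statements that the article does make.

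A reader might go further and conclude that MARS is the outcome more open to reporting bias and should be replaced by refill data available in both arms. The article does not support that. DRP identification also draws on a structured patient interview (Primary outcome measures), so the ranking is not established. The dispensing profile ("This profile shows when the patients has obtained his medication from the pharmacy") is described for the intervention group's medication review. The pharmacy-system records mentioned under Primary outcome measures and Costs effectiveness make similar control data plausible, but they do not mention dispensing dates.

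**Conclusion.** The point holds as a contradiction between the Abstract and the Sample size section, with a consequence that depends on the unstated success rule. If either outcome suffices, the two-sided family-wise error is up to about 10%: 9.75% under independence, 9.1% at correlation 0.5, and lower at higher correlation. False claims of benefit total 4.5-4.9% over the same range of correlation (0 to 0.5), against 2.5%. If both are required, the error is at most 5%, but the 80% power does not describe the trial because adherence was never powered.

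These figures assume two-sided tests at 0.05 for each outcome and both null hypotheses true. A reader might infer that the trial simply has a 9-10% false positive rate. The article does not support that, because it states no either-suffices rule. The matter should be settled because it decides what counts as a positive trial, and wording is enough to settle it.

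**What to change.** Make DRP occurrence the single primary outcome, as the Sample size section and the main objective already assume. Amend the Abstract and the Outcome Measures section to match. Test MARS adherence second in a fixed sequence: confirmatory at two-sided 5% if the DRP comparison is significant at 5%, and descriptive otherwise. This keeps the family-wise error at or below 5% and leaves the full 5% with DRPs.

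The Discussion reports inclusion as done between January 2008 and March 2009. Moving a declared primary outcome at that stage is a substantive change even though only words alter. Make it before outcome data are analysed, date it, and disclose it with the reason.

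**Cost.** No patients are added. Adherence alone can no longer make the trial positive, and it is barred from confirmatory testing whenever DRPs are not significant. That could happen often. If 342 really is the total, power for 30% against 20% is about 57% ignoring clustering, and 50-51% if the 15% allowance is read as a sample-size inflation.

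**Alternative.** Splitting the error 0.025 + 0.025 keeps both outcomes primary. It raises the DRP requirement from 588 to 712 in total before clustering (712/588 = 1.21). At 342 in total, it leaves about 46% power for DRPs ignoring clustering, or 39-40% with the allowance.

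Refill adherence can be reported beside MARS as an optional supporting measure, but only if dispensing dates are confirmed to be available in both arms.

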**Discussion:**

Combining both medication review and Cognitive Behaviour Treatment may decrease DRPs and may result in more compliance with drug use among patients discharged from the hospital and using 5 or more chronic drugs.

**Trial registration:**

Dutch Trial Register NTR1194

## Background

Drug related problems (DRPs) are events or circumstances involving drug therapy that actually or potentially interfere with desired health outcomes [1]. Examples of DRPs are contra-indications, interactions, adverse drug reactions (ADR) and inefficacy of treatment. Causes for these problems can be prescription errors, non-compliance with treatment and the specific effects of drugs in patients. Factors that increase the risk of DRPs are polypharmacy, co-morbidity, aging, non-adherence and lack of coordination between different treating physicians.

An increased number of prescribed drugs (polypharmacy) strongly increase the risk of DRP. Runciman found a correlation between increases in medication use and rates of adverse drug reactions associated with hospitalization [2]. Another recent review of studies of the effect of polypharmacy on the health state of elderly people has shown that multiple drug use is a strong predictor of hospitalisations, nursing home placement, death, hypoglycaemia, fractures, impaired mobility, pneumonia and malnutrition [3]. Furthermore, Leendert et al suggest that elderly people have a higher risk of hospitalisation caused by DRP, especially if they use have 4 or more co-morbidity [4].

Elderly people >75 year seem at higher risk for hospitalisation caused by DRP [2]. A study conducted in the Netherlands examined the occurrence of hospitalisations that were related to medication. This study showed 12.793 acute hospital admissions per year of which 714 admissions were medication related and 332 of these admissions were preventable. They calculated that 19.000 hospital admissions per year were related to medication and were preventable [4]. Specific risk factors were the number of prescribing physicians [5] and the number of diagnoses [6], the number and combination of several (inappropriate) drugs [6,7] and the use of inappropriate drugs [8-11].

Non-adherence is another risk factor for the occurrence of DRP. Assuming that drugs have been prescribed correctly, non-compliance may substantially affect the efficacy of treatment or even enhance the risk of side effects [12-14]. In the Dutch population 50% of the patients were shown to discontinue the use of chronic medication within one year after initiation. Discontinuation of chronic medication depended on the type of chronic medication and occurred frequently among patients who were using antihypertensive medication, cholesterol lowering drugs, anti-osteoporoses drugs, anti-rheumatic medications and antidepressants [15].

Hospitalisation can also be the cause of DRP. Hospitalisation and subsequent discharge are associated with discontinuity of care [16]. At the point of discharge the use of certain drugs may have been discontinued and the doses of others changed while new medication may have been added. In the Netherlands, pharmacists use a computerized system to detect drug problems among their patients. This system fails to detect all drug problems and does not provide information on problems with medication use, which elderly patients may experience. In the present study, pharmacists will perform a medication review on elderly patients discharged from the hospital. This medication review is a structured, critical examination of patient's medicines with the objective of reaching an agreement with the patient about treatment, optimising the impact of medicines, minimising the number of medication-related problems and reducing waste [17].

A systematic review conducted by Royal et al. concluded that there was evidence showing that pharmacist-initiated interventions including a medication review component are effective in reducing hospital admissions by 36%. Several studies have shown that cognitive behaviour treatment can be useful in improving medication adherence among patients [18,19]. Patients may benefit of changes in attitude to medication, resulting in increased compliance with drug use.

The present randomized controlled study aims to improve pharmacotherapy by means of combining two effective strategies including medication review and cognitive behaviour treatment. To our knowledge, the effect of combining both methods to minimize drug related problems and improve compliance among elderly patients discharged from the hospital has not been studied previously.

### Theoretical framework the cognitive behavioural approach

Studies have shown that a change in patients attitude to medications may enhance adherence to medications [16-20]. Behavioural interventions may increase this effect [16-20]. A behavioural model of medication adherence is shown in figure 1. This model is based on the Theory of Planned Behaviour and provides insight into the factors that may determine adherence behaviour [18,19]. Patients gain 'treatment experience' once they are exposed to a medical regimen. To enable patients to adequately make informed choices about their behaviour and to motivate themselves to execute the behaviour correctly and at the right time, patients must possess a basic level of understanding about their illness. Health care professionals must communicate this information in understandable and concrete language, tailored to the needs of each specific patient [19]. The most important concept used in the adherence model is the intention of the patient to adhere to the medical recommendations. The Theory of Planned Behaviour states that the intention to adhere is determined by the subjective norm, the attitude and the perceived behavioural control [18]. The subjective norm is what a person thinks other people believe (s) he should do (e.g. physicians or partners) and the motivation to comply with these normative references. The subjective norm of a patient can be changed through either changing the patients perception of the norm, or through changing the patients motivation to comply with this norm.

**Figure 1 F1:**
[figure not shown]
**Model for Medication Adherence: theory of planned behaviour**.

The attitude reflects salient beliefs about the perceived outcomes of these behaviours (e.g. adherence leads to better health than non-adherence) and the evaluations of these outcomes (e.g. good health is essential for living longer). It is important for the patient to realise that the benefit of adhering to the medical regimen outweigh the costs. It is therefore important that doctors and community pharmacists explain to the patient what the benefits are of medication adherence. The patient will then be able to make his own informed choice about his medicines and outweigh the costs of this behaviour.

The last component is the perceived behavioural control (PBC). The PBC has two components: self-efficacy dealing with the perceived ease or difficulty of performing behaviour, such as feeling confident to always take medication correctly in a private setting and controllability the extent to which the behaviour is up to the person. If a person has a demanding job it is sometimes difficult to remember intake or have some privacy. To optimize someone's PBC, it is useful to separate behaviour in small and simple steps and to facilitate the behaviour where possible (for example: use dose organizers) and plan the execution of the behaviour in a setting in which the patient feels confident about correctly performing the behaviour on a daily basis.

The outcome of the attitude, subjective norm and perceived behaviour control is expressed in a behavioural intention. This intention leads to accepting or refusing adherence to the treatment as prescribed [19].

### Medication review

Medication review is an intervention that can be used to prevent the occurrence of DRP. Medication review requires access to the patients notes, full record of prescriptions and non-drug care and results from laboratory tests etc. The medicines used by the patient will be reviewed in the context of the patients condition and the perspective of the patient. In this process the patient is involved as a full partner. This means listening to the patient's views and beliefs about their medicines, reaching an honest understanding of their medicine taking behaviour and taking full account of their preferences in any decisions about treatment. Possible detected DRPs are communicated with the prescriber, in order to find a solution for these problems. Any changes made will then be communicated with the patient.

### Cognitive behaviour treatment

To increase concordance with drug use, according to our theoretical framework, we have developed a combined intervention with motivational interviewing (MI) and Problem Solving Treatment (PST). MI is used to increase patient's motivation towards concordance with medication prescription [21]. When patients experience barriers with medication use, PST will be used in order to give patients the tools to overcome these barriers [22].

#### Motivational interviewing

Motivational interviewing is a client-oriented counselling method that is shown to be effective in improving health behaviour [21]. Increasing the intrinsic motivation of patients can then lead to a positive behavioural change. During the counselling sessions the therapist does not take an expert role but rather a role as a partner. MI includes 5 counselling techniques aimed at helping patients resolve ambivalence about health behaviour: (1) expressing empathy; (2) developing discrepancy; (3) avoiding argument (4) rolling with resistance; and (5) supporting self-efficacy [21]. When patients are motivated to change their health behaviour, the next step is to increase their self-management towards this behaviour by using PST.

#### Problem solving treatment

This intervention increases the ability of patients to solve their problems in a structured way and improve their confidence in dealing with future problems. The treatment aims to give patients the tools to overcome barriers in order to stimulate structural healthy behaviour. During the treatment session there is an active collaboration between the patient and the pharmacist, in which the patient takes an active role in the planning of his treatment [23]. PST can be considered as a series of 7 stages [22].

1. Explanation of the intervention and its rationale

2. Definition and breaking down of the problem

3. Establishing achievable goals for the problem resolution. Achieve goals are SMART goals: Specific, Measurable, Achievable, Relevant, Timed

4. Generating multiple possible solutions

5. Evaluating and choosing the solution

6. Implementing the preferred solution

7. Evaluating the outcome

